# Efficacy and Safety of Modified Yupingfeng Nasal Spray in Controlling the Recurrence of Persistent and Moderate-Severe Allergic Rhinitis: Study Protocol for a Multicenter, Open-Label, Randomized, and Parallel-Arm Trial

**DOI:** 10.1155/2022/4666332

**Published:** 2022-08-10

## Abstract

**Background:**

Recurrent episode of allergic rhinitis (AR) is one of the leading illnesses that affects patients. However, there is little research evidence to support pharmacotherapy for AR recurrence. Therefore, this study was designed to explore the efficacy of pharmacotherapy in the control of the recurrence of AR.

**Methods:**

In this study, a multicenter, open-label, randomized, and parallel-arm trial will be conducted at three study centers. A total of 190 subjects aged 18–65 with persistent and moderate-severe AR (Qi deficiency and blood stasis syndrome) will be randomly assigned to receive the modified Yupingfeng nasal spray or mometasone furoate aqueous nasal spray. When subjects' rhinitis control assessment test (RCAT) score is >21 for two weeks, they will stop taking the medication and enter the follow-up. Once a relapse occurs, the time point will be recorded, and the follow-up stops. The primary outcome is the six-month recurrence rate of AR after intervention withdrawal. The secondary outcomes are the one-month recurrence rate of AR, the RCAT score, the duration of follow-up, the duration of medication, the nasal endoscopic results, and questionnaires to evaluate symptoms, signs, and quality of life. The mechanism outcomes include some indicators that may be associated with AR recurrence. In addition, electrocardiograms and other safety indicators will be applied to evaluate the drug's safety. *Discussion*. This is the first study to explore the efficacy of traditional Chinese medicine nasal spray on AR from the perspective of controlling recurrence. The results of this trial may provide valuable clinical evidence for controlling the recurrence of this disease by pharmacotherapy. *Trial Registration*. This study was registered with registration number ChiCTR2100047053 (Chinese Clinical Trial Registry, https://www.chictr.org.cn/showproj.aspx?proj=127432 on June 7, 2021).

## 1. Introduction

Allergic rhinitis (AR) is one of the most common allergic diseases worldwide and it is a global health problem affecting 40% of the world's population [1]. The prevalence of AR has been increasing worldwide since the 1960s [2] and has dramatically increased in recent years [3]. For example, AR showed a sharp increase in prevalence from 11.1% to 17.6% over 6 years in major Chinese cities [4]. The repeated attacks of AR are one of the main difficulties faced by patients. A study of 7-year-olds in South Korea found that the two-year recurrence rate for AR is 72% [5].

The pharmacotherapy of AR includes corticosteroids, antihistamines, and decongestants, most of which focus on suppressing immune factors and controlling immediate symptoms. Even though pharmacotherapy has proven to be highly effective in controlling allergic symptoms, most of the pharmacological management approaches recommended in the guidelines for AR have not been evaluated for efficacy in controlling recurrences. Furthermore, their long-term use can cause side effects, including epistaxis, mucosal dryness, and other adverse reactions, reducing patient compliance. Globally, while the standard pharmacotherapy of AR is relatively mature, the prevalence of AR is still rising [6, 7], and the recurrence rate is still high [8], making it urgent to find new therapies to solve this problem.

The efficacy and safety of traditional Chinese medicine (TCM) have been confirmed in the treatment of AR [9, 10]. According to a meta-analysis, four studies showed that the recurrence rates of AR at three and six months in the TCM groups were significantly lower than those in the control groups [11]. Another meta-analysis reached the same conclusion in children [12]. Yupingfeng powder (YPF) is a classic prescription for treating unsolidified lung-defense Qi syndrome and has shown profound effectiveness in clinical practice in regulating histological morphology, immune factors, and inflammatory cytokines of AR [13, 14] and in treating recurrent respiratory diseases [13, 15, 16]. In TCM, unsolidified lung-defense Qi syndrome is the basic pathogenesis of AR. AR patients generally have a long-term course and high relapse possibility. TCM believes that prolonged illness and repeated attacks of the disease can lead to the formation of blood stasis. In the clinic, symptoms of blood stasis such as narrower diameter, swelling turbinate, and purple and thick veins under the tongue are quite common in AR patients with recurrent attacks. Therefore, Qi deficiency and blood stasis syndrome (QDBS) is a core TCM syndrome of AR recurrence. Based on YPF, modifications have been made to strengthen its function of activating the blood and opening orifices, making it more suitable for AR with recurrent attacks. Although its oral administration is effective, it is not conducive to the rapid relief of AR symptoms due to its limitations, such as slow absorption, easy decomposition by digestive enzymes, and metabolism through the digestive tract and liver [17].

Therefore, the modified YPF has been made into a nasal spray named the modified Yupingfeng nasal spray (MYN), which has the function of “replenishing lung Qi to consolidate exterior and activating blood to open the orifice.” In more than two decades of clinical and animal research, previous studies have shown that MYN can effectively improve the symptoms of AR patients and animal models, reduce the expression of inflammatory factors, regulate immune homeostasis, improve blood stasis, and repair the epithelial barrier of the nasal mucosa [18–23]. Most importantly, we observed that the 4-week follow-up recurrence rate was lower in the MYN group than in the mometasone furoate aqueous nasal spray group [23]. However, that trial was a small, single-center trial with poor quality, which was not conducive to providing high-quality evidence for the efficacy of pharmacotherapy in controlling recurrences of AR. Therefore, a multicenter, open-label, randomized, and parallel-arm trial will be conducted to provide evidence for the efficacy and safety of MYN in the treatment of persistent and moderate-severe AR (QDBS) in the control of recurrence and to explore its possible mechanism.

## 2. Methods

### 2.1. Objectives

The recurrent attacks of AR are one of the main issues that affect patients. However, most of the pharmacological management approaches recommended in the guidelines of AR have not been evaluated for their efficacy in controlling recurrences. Our previous clinical observations showed that MYN achieved several advantages in treating allergic rhinitis, especially in controlling recurrences. Therefore, this study was designed to provide more substantial evidence for the efficacy and safety of MYN in preventing the recurrence of AR.

### 2.2. Trial Design

We will conduct a multicenter, open-label, randomized, and parallel-arm trial among persistent and moderate-severe AR patients (QDBS), and the ratio of the experimental group to the control group will be 1 : 1. In this study, MYN will be applied to the experimental group, while mometasone furoate aqueous nasal spray will be applied to the control group. The six-month recurrence rate of AR after withdrawing the intervention will be the primary outcome to evaluate the efficacy and safety of MYN in the treatment of recurrence of persistent and moderate-severe AR (QDBS), and this study will also explore its possible action mechanism. We present the protocol in accordance with the Standard Pprotocol Items: Recommendations for Interventional Trials (SPIRIT) reporting checklist (S1). The study flowchart is shown in Figure 1.

### 2.3. Study Setting

Subjects will be enrolled in three comprehensive third-grade first-class hospitals: the Hospital of Chengdu University of Traditional Chinese Medicine, the West China Hospital of Sichuan University, and the Sichuan Provincial Hospital of Integrated Traditional Chinese and Western Medicine (two of them are academic hospitals).

### 2.4. Participants and Recruitment

#### 2.4.1. Diagnostic Criteria of AR

AR belongs to the category of “Biqiu” in TCM [1]. The diagnostic criteria of “Biqiu” will refer to “Otolaryngology of Traditional Chinese Medicine [24].” The Western diagnostic criteria and grading standards for AR will refer to the ‘Chinese Society of Allergy Guidelines for Diagnosis and Treatment of Allergic Rhinitis [1]'. The details are given:Subjects who have typical AR nasal symptoms (nasal itching, rhinorrhea, sneezing, and nasal obstruction) and can have ocular symptoms (ocular grittiness/itching/redness and ocular tearing)Watery nasal discharge, edematous and pale nasal mucosa, and swollen inferior turbinatePositive skin response to house dust mites (HDM) (++ and above) in the skin prick test (SPT)Persistent AR (frequency of symptoms ≥4 days/week and ≥4 weeks/year)Moderate-severe AR (symptoms have a significant impact on quality of life)

#### 2.4.2. Diagnostic Criteria of QDBS

Syndrome element is the minimum diagnostic unit of TCM syndrome diagnosis. QDBS is a combination of “Qi deficiency” and “blood stasis” syndrome elements [25]. According to the diagnostic criteria of “Qi deficiency” and “blood stasis” from the “Guiding Principle for Clinical Study of New Chinese Medicines [26] the syndrome differentiation criteria are given in Table 1. Each center has a Chinese medicine expert who will evaluate TCM syndromes of the participants.

### 2.5. Eligibility Criteria

The inclusion criteria and exclusion criteria are given in Table 2.

### 2.6. Sample Size

In this study, the 6-month recurrence rate was used as the basis for sample size estimation. Combined with our previous research and the literature, the six-month recurrence rates of AR treated with MYN and mometasone furoate aqueous nasal spray were approximately 50% and 75% [27], respectively. Using 5% as the superiority margin, an acceptable alpha of 2.5% (one-tailed), and an acceptable beta of 20%, 86 participants were required in each group. To allow for a 10% loss to follow-up, we will recruit 190 subjects in total.

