#### 2.10.2. Primary Outcomes

The primary outcome is the six-month recurrence rate of AR after intervention withdrawalFollow-up: subjects will enter the follow-up period after withdrawal of medications. Once a relapse occurs, the patient's recurrence time will be recorded, and the follow-up ends. Otherwise, the follow-up will continue until six months after drug withdrawal.Definition of recurrence/relapse: when the RCAT score ≤21 during follow-up, the patient will be considered in a relapse stateDefinition of six-month recurrence rate: six-month recurrence rate = number of recurrent AR patients in six months/total number of patients × 100%The RCAT has sufficient reliability, validity, and responsiveness and is a simple patient self-assessment scale [29]. RCAT can be used to assess a patient's rhinitis control status in clinical practice [30]. During the treatment stage, we will collect the RCAT scale online once a week, and during the follow-up stage, we will collect the RCAT scale online every two weeks.

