### 2.12. Statistical Methods

All analyses will be based on the intention-to-treat (ITT) principle. Missing data will be reduced to a minimum. For data loss caused by subject drop-out, data from the previous measurement will be carried forward. The frequency, percentages, means and standard deviations, medians, and quartiles will be calculated for descriptive analysis. Intergroup comparisons of continuous variables will be performed using the *t*-test or Mann–Whitney *U* test. Categorical variables will be compared using Pearson *χ*^2^ tests or Fisher exact tests. Time-to-event outcomes will be analyzed using the Kaplan–Meier method and Cox proportional hazard models. Two-tailed *p* < 0.05 will be considered statistically significant for all analyses. All statistical analyses will be conducted using SPSS version 25.0 for Windows (IBM Corporation, Armonk, NY, USA).

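### The sample size assumes superiority by more than a 5-point margin, but the stated analysis tests only for a difference from zero

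*Protocol article*

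**What the plan says.** The primary outcome is a proportion. Section 2.10.2 defines it as "six-month recurrence rate = number of recurrent AR patients in six months/total number of patients", expressed as a percentage.

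Section 2.6 (Sample Size) bases the calculation on that outcome. The assumed six-month rates for MYN and "mometasone furoate aqueous nasal spray were approximately 50% and 75% [27], respectively". The remaining inputs are: "Using 5% as the superiority margin, an acceptable alpha of 2.5% (one-tailed), and an acceptable beta of 20" per cent. The result is 86 per group, raised to 190 in total for 10% loss to follow-up.

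Section 2.12 (Statistical Methods) assigns tests by type of variable. "Categorical variables will be compared using Pearson" chi-square or Fisher exact tests, and two-tailed p < 0.05 "will be considered statistically significant for all analyses". It gives no margin, no shifted null hypothesis and no confidence-limit rule. The margin occurs only in section 2.6.

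**The concern.** A superiority margin in a sample size calculation implies a hypothesis: the control rate minus the MYN rate is at most 5 points under the null and more than 5 points under the alternative. Pearson's chi-square and Fisher's exact test have a different null, namely equal rates. The article therefore contains two success criteria for one primary outcome.

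A result between the two thresholds is positive under section 2.12 and negative under section 2.6. If both stand, the choice could be made after the data are seen. If section 2.12 is simply followed, the margin that determined the sample size is dropped and the stated power describes a test that will not be run.

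**Working it through.** **Inputs.** From section 2.6: p(MYN) = 0.50, p(control) = 0.75, margin 0.05, one-sided alpha 0.025 (z = 1.96), beta 0.20 (z = 0.8416). From section 2.2: 1:1 allocation. From section 2.12: chi-square or Fisher, two-tailed 0.05.

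**1. Reproducing 86 per group.** With unpooled variance,

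n = (1.96 + 0.8416)² × [0.50 × 0.50 + 0.75 × 0.25] / (0.25 − 0.05)² = 7.849 × 0.4375 / 0.04 = 85.85, so 86.

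The stated figure is reproduced, with the 5% read as an absolute difference.

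**2. The same calculation without the margin.**
- Unpooled: 7.849 × 0.4375 / 0.25² = 54.9, so 55.
- Pooled null variance, which is the form that matches chi-square: [1.96 × √(2 × 0.625 × 0.375) + 0.8416 × √0.4375]² / 0.25² = 57.7, so 58.
- With continuity correction: 66.

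None gives 86. The margin is what produced the sample size.

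**3. Power at 86 per arm under 75% vs 50%.** The standard error under the alternative is √(0.4375/86) = 0.0713.
- Margin test: Φ(0.20/0.0713 − 1.96) = 80.1%; exact binomial enumeration gives 79.6%.
- Chi-square against zero: Φ[(0.25 − 1.96 × √(0.46875/86)) / 0.0713] = 93.0%; exact 93.0%.

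**4. Smallest observed difference that succeeds, 86 per arm, 64 control recurrences (74.4%).**
- Chi-square: 64 vs 51. The difference is 13/86 = 15.1 points, 95% CI 1.2 to 29.0. This is significant against zero but does not exclude a benefit of 5 points or less.
- Margin test: 64 vs 47. The difference is 17/86 = 19.8 points, lower limit 5.8.

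**5. How often the rules disagree (exact enumeration, 86 per arm).** The margin test is taken as the lower limit of the two-sided 95% Wald interval above 5 points.

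| True rates, control vs MYN | Chi-square favours MYN | Margin test succeeds | Chi-square succeeds, margin test fails |
|---|---|---|---|
| 75% vs 50% | 93.0% | 79.6% | 13.3% |
| 75% vs 60% | 55.8% | 30.2% | 25.6% |
| 75% vs 65% | 30.1% | 11.4% | 18.6% |
| 75% vs 70% | 11.1% | 2.7% | 8.4% |

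The last row lies on the boundary of the margin null, where the design allows 2.5%.

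**6. If all 190 are analysed (95 per arm).** Exact power at the design rates is 95.1% for chi-square and 83.5% for the margin test. At 75% vs 70% the success rates are 11.7% and 2.7%. The thresholds are 71 vs 58 (13.7 points) and 71 vs 53 (18.9 points). The picture is the same.

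**The case against.** The strongest reply has four parts.

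- **The written test is valid for its own claim.** With equal rates of 75% and 86 per arm, chi-square favours MYN in 2.5% of trials. The 11% at 75% vs 70% is then power to detect a real, small benefit. This stands: it is an error rate only against the margin null. But that is the null that produced 86 per group.
- **No one is short-changed on numbers.** The trial has more power for the written test than it states, and no estimate is biased. This also stands. The harm is to the meaning of a positive result, and a published confidence interval would let readers check the margin for themselves. It would not say which rule the trial was committed to.
- **The claim of more than 5 points is inferred.** The objectives speak of efficacy in preventing recurrence, and section 2.6 writes out no hypothesis. That is true, but a superiority margin has no other meaning in a sample size formula, and the arithmetic confirms how it was used.
- **The full protocol or analysis plan may hold a margin test.** Section 2.12 is a general paragraph that does not name the primary outcome. However, it fixes its significance rule for all analyses. A plan that tested the margin would depart from the chi-square or Fisher test stated there; a plan that followed section 2.12 would abandon section 2.6. The issue is two stated rules that conflict, not a detail left out.

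Sidedness is not at fault: one-sided 2.5% and two-sided 5% share the same critical value in the favourable direction.

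**Conclusion.** The concern holds; the plan is wrong as written. At 86 per arm with control recurrence near 75%, observed differences from 15.1 points up to just below 19.8 points pass the analysis rule and fail the design rule. If the true rates were 75% vs 60%, about a quarter of trials would end there. The 80% power does not describe the written test, whose power at the design rates is about 93%.

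These figures assume the rates in section 2.6, an absolute 5-point margin, and a Wald interval for the margin test. The conclusion does not depend on whether 86 or 95 per arm are analysed. It concerns the success criterion for the primary outcome, not the adequacy of the sample size.

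**What to change.** Choose one rule and state it in both sections before any outcome data are analysed.

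- **Keep the margin (preferred, since it is the design that was sized).** Add to section 2.12 that superiority on the primary outcome is declared only if the lower limit of the two-sided 95% confidence interval for six-month recurrence, control minus MYN, exceeds 5 percentage points. The sample size need not change: power is about 80% at 86 per arm and about 84% at 95. The cost is one sentence and a stricter bar than p < 0.05.
- **Test against zero.** Delete the margin from section 2.6 and restate the power as about 93% at 86 per arm (about 95% at 95 per arm). The cost is that a significant result supports only some benefit, not one above 5 points.

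Either is sound. The change should be recorded as an amendment, dated before analysis.

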### 2.7. Recruitment

To ensure adequate participant enrollment, participants will be enrolled in the outpatient department of each center, simultaneously. Participants will also be recruited through advertisements.

### 2.8. Randomization and Blinding

This study adopted a multicenter, open-label, randomized, and parallel-arm controlled design. The randomization method was stratified block randomization. The patients were stratified based on the three different centers, and the ratio of the experimental group to the control group was 1 : 1. According to the given number of seeds and the appropriate length of the segment selected, an independent clinical statistician will use SAS 9.4 statistical software to generate a random sequence and save it as a file in a sealed envelope and then distribute the corresponding envelopes to each center. An independent statistician will keep all of the methods, processes, results, and envelopes of the random sequence. After the beginning of the study, the envelopes will be opened in order of grouping, and recruited subjects will be assigned to treatment groups according to the information in the envelope. Any randomized subject will retain their randomization number after withdrawing from the study for any reason. The random number corresponding to this subject will not be allowed to be reused by other new subjects. Only outcome assessors, examiners, and data analysts will be blinded in this study. Subjects and researchers will not be blinded due to the differences in the color and odor between MYN and the mometasone furoate aqueous nasal spray.

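### Randomisation is stratified by centre, but the tests named for the primary outcome cannot take centre into account: a minor loss of efficiency if centres differ in recurrence

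*Protocol article*

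**What the plan says.** **Design.** Section 2.8 of the protocol article states: "The randomization method was stratified block randomization". Centre is the only stratification factor ("The patients were stratified based on the three different centers"), and "the ratio of the experimental group to the control group was 1 : 1".

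**Primary outcome.** Section 2.10.2 defines a proportion: "six-month recurrence rate = number of recurrent AR patients in six months/total number of patients".

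**Analysis.** Section 2.12 names methods by type of variable. "Categorical variables will be compared using Pearson" chi-square or Fisher exact tests. Continuous variables get a t-test or Mann-Whitney U test. Time-to-event outcomes get Kaplan-Meier and Cox models, with no covariate or stratum listed. Centre appears nowhere in the section, and no confidence interval for the primary difference is mentioned.

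**Sample size.** Section 2.6 assumes recurrence rates for the experimental spray and "mometasone furoate aqueous nasal spray were approximately 50% and 75% [27], respectively". It adds "Using 5% as the superiority margin" and "an acceptable alpha of 2.5% (one-tailed"), with 80% power, 86 per group and 190 in total. Centre does not enter this calculation.

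**The concern.** Blocks within centre force the two arms to be close to equal in size at each site. Differences between sites in recurrence then largely cancel out of the treatment comparison. A Pearson test does not know this: its variance is built from the pooled recurrence rate and still includes the between-centre variation. If centres differ, the standard error is therefore too large, the true type I error falls below the nominal 5%, and some power is given away.

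Section 2.12 does name its tests, and neither Pearson nor Fisher can carry a centre term. So for the primary outcome the mismatch lies in a stated method and is not merely a detail left open. What is at stake is efficiency and agreement between design and analysis, not protection against a false positive.

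**Working it through.** **1. The plan's own figure.** Inputs from section 2.6: rates 0.50 and 0.75, margin 0.05, one-sided alpha 0.025, power 0.80.

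n per arm = [0.50×0.50 + 0.75×0.25] × (1.960 + 0.842)² / (0.25 − 0.05)² = 0.4375 × 7.849 / 0.04 = 85.85, rounded up to 86.

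86 × 1.10 = 94.6, so 95 per arm and 190 in total. The stated figures reproduce, without centre.

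**2. Expected size of the conservatism.** The article gives no centre-specific recurrence. Assumption: three equal centres, mean recurrence 62.5% (midway between 50% and 75%), centre rates at −d, 0 and +d from that mean.

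- Variance used by the pooled test: 0.625 × 0.375 = 0.2344 per patient.
- Between-centre part that the design removes: 2d²/3.
- Ratio r = 1 − (2d²/3)/0.2344.
- True two-sided error of the unstratified test ≈ 2 × [1 − Φ(1.96/√r)].

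| d | 2d²/3 | r | 1.96/√r | true error |
|---|---|---|---|---|
| 0 | 0 | 1.000 | 1.960 | 5.0% |
| 0.10 | 0.0067 | 0.972 | 1.988 | 4.7% |
| 0.20 | 0.0267 | 0.886 | 2.082 | 3.7% |
| 0.25 | 0.0417 | 0.822 | 2.161 | 3.1% |

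**3. Simulation on the same scale.** 95 per arm, with 32, 32 and 31 per centre and exact 1:1 balance within centre. Power is for an assumed 20-point effect, smaller than the protocol's 25. Error ranges cover separate runs; power is from one run.

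| d | Pearson type I error | Power, Pearson | Power, CMH |
|---|---|---|---|
| 0 | 5.0% | 81.9% | 81.5% |
| ±10 points | 4.7–4.8% | 82.2% | 83.0% |
| ±20 points | 3.6–3.8% | 83.3% | 86.3% |
| ±25 points | 3.0–3.2% | 84.1% | 88.9% |

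The CMH type I error was between 4.8% and 5.0% throughout.

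**4. Simulation under the protocol's own effect.** Overall rates 50% and 75%, 95 per arm, centre log-odds shifted by −s, 0, +s (s is again an assumption). Each power column gives unstratified, then centre-stratified. The margin test sets the difference against 5 points.

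| s | control rates by centre | type I error, unstratified | power against no difference | power of margin test |
|---|---|---|---|---|
| 0 | 75/75/75% | 5.0% | 95.1%, 94.9% | 83.3%, 83.2% |
| 0.25 | 70/75/80% | 4.9% | 95.3%, 95.3% | 83.6%, 83.6% |
| 0.5 | 66/76/84% | 4.6% | 95.5%, 95.8% | 83.9%, 84.3% |
| 1.0 | 57/78/91% | 3.6% | 96.1%, 97.1% | 85.1%, 87.7% |
| 1.5 | 49/81/95% | 2.3% | 97.0%, 98.6% | 86.8%, 91.7% |

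At s = 1.0 the mean unstratified standard error is 0.0675 against a true 0.0635; the stratified one is 0.0634. Unequal centres (50, 25 and 20 per arm) show the same pattern.

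**The case against.** The case against has real force.

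- **Left to the analysis plan.** The article is condensed, and section 2.12 is one short paragraph for all outcomes. A full protocol or analysis plan may add centre. This stands for the Cox model, where no strata or covariates are listed at all. It stands less well for the primary outcome, because the tests that are named exclude centre.
- **Conditional effect.** The loss arises only if centre predicts recurrence, and the article gives no figure for that. The ±20 and ±25 scenarios mean gaps of 40 and 50 points between the extreme centres. Below that the effect is small. This stands.
- **Weak grounds for expecting large differences.** A reader might infer that the Chinese-medicine expert at each centre (section 2.4.2) makes outcomes differ by site. That expert judges the syndrome for entry. Relapse is a self-rated score on the rhinitis control assessment test, collected online (section 2.10.2). Eligibility criteria and operating procedures are shared.

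Three stronger readings are tempting and not supported:

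- That the primary result would be invalid or the trial underpowered. The error is on the conservative side, and under 50% versus 75% with 95 per arm power stays above 80% in every scenario run. Unstratified power even rises with the spread; the stratified test simply gains more.
- That every planned test ignores centre. The Cox model is left unspecified in this respect.
- That the primary confidence interval is too wide. Section 2.12 states none. An unstratified interval would be too wide only under the same condition.

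**Conclusion.** The mismatch is real and minor. The tests named for the primary outcome do not reflect the stratified randomisation, and where centres differ in recurrence they are conservative and somewhat less powerful than they need be. In the assumed 20-point-effect scenario the power loss is under 1 point at a ±10-point spread and about 3 points at ±20. Under the protocol's own 25-point difference, the loss is at most 0.4 points for log-odds shifts up to 0.5. At a shift of 1.0 it is about 1 point (test of no difference) to 2.6 points (margin test). Every one of these figures rests on an assumed spread between centres. The direction does not depend on the spread chosen, apart from the negligible cost of stratifying when there is none.

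**What to change.** - Make the primary analysis centre-stratified: a CMH test, with a centre-stratified risk difference and its 95% confidence interval set against the 5-point margin of section 2.6. The two-sided 95% interval matches the one-sided 2.5% alpha used there.
- For time to relapse, stratify the log-rank test that accompanies the Kaplan-Meier curves, and the Cox model, by centre.
- Keep the unstratified Pearson or Fisher test as a sensitivity analysis.

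**Cost:** wording only, settled before the data are analysed. Centre is known for every patient because it defines the randomisation strata, and the sample size need not change. If centres turn out not to differ, the price is under 0.5 points of power.
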